### Randomisation

HCPs will be assigned to one of the four clusters. The clusters sequentially receive the intervention, and the moment of intervention rollout within one cluster the unit of randomisation is (Fig. 1). Randomisation is performed by means of computer-generated allocation. Patients are blinded to group assignment.

The allocation is not concealed from HCPs or for the researchers, because the start of the intervention (i.e., organising or receiving the CME training) is an obvious point in time that does not lend itself for blinding. An independent research assistant will perform the allocation sequence, enrolling of participants, and assignment of participants to groups.

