### Study design

This study is a stepped-wedge cluster-randomised controlled trial. A multifaceted implementation strategy for the Dutch multidisciplinary care guideline for nonspecific LBP will be compared to passive dissemination of the guideline. The implementation strategy will be targeted at both health care professionals (i.e., GPs, OPs and PTs) and patients. The HCPs are allocated to one of four clusters, which are compiled based on the HCPs’ geographic proximity to each other. This grouping allows for minimisation of contamination between the participating HCPs. A stepped-wedge design is applied to assure stepwise implementation of the guideline in all of the participating HCPs (Fig. 1). Patients are allocated according to their GP/PT allocation, i.e., patients registered within a practice that is in the control group at time of enrolment will automatically be allocated into the control group for patients.

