#### Patients

Five hundred patients with LBP will be included to participate in this study. All patients registered in the practices of participating GPs and PTs receive an information leaflet about this study, and a recruitment letter from their GP/PT. Furthermore; PTs have information and recruitment posters and leaflets in their practices. Patients interested in participation can apply directly via e-mail or using a postal reply card at the research assistants’ office, where eligibility criteria are assessed prior to inclusion.

Patients are eligible if they have a minimum age of 18 and a maximum age of 75 years, have access to the Internet, have visited their GP or PT due to back complaints no later than 3 months prior to inclusion, and are diagnosed with nonspecific LBP. Nonspecific LBP is defined as low back pain (with or without motor and/or sensory deficits in one or both legs) that is not caused by underlying specific pathology (red flags), i.e., a tumour, (osteoporotic) vertebral fracture, ankylosing spondylitis, and cauda equina syndrome.

Patients having the following characteristics will be excluded from this study: serious long existing comorbidity, i.e., Alzheimer’s disease, Multiple Sclerosis, Parkinson’s disease, ALS, CVA (diagnosed 1 year prior to inclusion up to moment of inclusion), confirmed pregnancy (identified 1 year prior to inclusion up to moment of inclusion), malignancy (diagnosed 5 years prior to inclusion up to moment of inclusion), and severe psychiatric disorders, i.e., schizophrenia and bipolar disorder.

In accordance with the local regulatory guidelines and standards for human subjects protection in the Netherlands (Medical Research Involving Human Subjects Act [WMO], 2005), and the assessment of the Medical Ethics Committee of the VU University medical centre, no written informed consent for participation was necessary to be obtained from participants.

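### One research-assistant role holds the rollout sequence and also enrols patients, so inclusion around a cluster's crossover can be decided with the arm already known

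*Protocol article*

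**What the plan says.** All of this is in the Protocol article.

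- **Randomisation.** Four geographic clusters cross over in a random order; the randomised unit is given as "the moment of intervention rollout within one cluster the unit of randomisation is". On concealment: "The allocation is not concealed from HCPs or for the researchers". The reason given is that organising or attending the training is visible. On roles: "An independent research assistant will perform the allocation sequence, enrolling of participants, and assignment of participants to groups". The sequence is computer-generated and patients are blinded.
- **Study design.** The patient's arm follows the practice: "patients registered within a practice that is in the control group at time of enrolment will automatically be allocated into the control group".
- **Participants, Patients.** All registered patients of participating GPs and PTs "receive an information leaflet about this study, and a recruitment letter from their GP/PT". Those interested apply by e-mail or reply card to the research assistants' office, "where eligibility criteria are assessed prior to inclusion". The visit for back complaints may lie up to 3 months before inclusion.
- **Statistical methods.** A crude and an adjusted longitudinal analysis are planned, both multilevel, with clusters as fixed effects.

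**The concern.** In a cluster trial that recruits patients after allocation, randomising the clusters does not protect the comparison of patients. That protection depends on inclusion being decided without regard to the arm. Here the article gives knowledge of the sequence and control of enrolment to the same role. The reason offered for leaving allocation open, a visible training session, holds for the providers and for those who organise the training. It does not explain why a person screening e-mails and reply cards must know a practice's status before deciding.

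At stake is the contrast on which a stepped-wedge design relies: the same cluster before and after its switch. If the patients included after the switch differ from those included before it, the difference in back beliefs partly reflects who was enrolled.

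**Working it through.** No figure of the plan is in dispute, so the check sets the sections side by side.

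1. **What fixes the arm.** By Study design, a patient is a control if enrolled before the practice's cluster crosses over, and otherwise an intervention patient. Three inputs decide this: the practice, the cluster's crossover date and the patient's enrolment date. The patient brings the first and randomisation sets the second. Only the third can be moved by the office.

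2. **Who controls that input, and what they know.** By Randomisation, the role that enrols also handles the sequence. By Patients, eligibility is settled at the research assistants' office before inclusion. As written, the role that sets the enrolment date knows the crossover date.

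3. **How much room there is.** The qualifying visit may precede inclusion by up to 3 months. A patient who visits and applies shortly before a crossover can therefore be included on either side of it, depending on how fast the application is handled. A long enough delay also takes the applicant past the 3-month limit. Away from a crossover, the only lever is rejection, and the criteria give little scope for it: age 18 to 75, internet access, a recent visit, an existing diagnosis, and named exclusions, several with stated time windows.

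4. **What the analysis removes.** For cluster c, write the expected score before the switch as a_c + s_c0 and after it as a_c + s_c1 + b. Here a_c is the cluster's stable level, b the effect, and s the contribution of who was included. The within-cluster contrast is

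   (a_c + s_c1 + b) − (a_c + s_c0) = b + (s_c1 − s_c0).

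   The fixed effect cancels a_c. It does not cancel s_c1 − s_c0. The adjusted analysis removes the part of that term explained by measured baseline factors; the crude analysis removes none of it.

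5. **Size.** The shift depends on the share of inclusions affected and on how far those patients differ from the rest. The article gives neither. For scale only, the planned effect is 0.10 × 26.5 = 2.65 points on the Back Beliefs Questionnaire. Assumed shifts between arms of 0.25, 0.5 and 1.0 point would be 0.25/2.65 = 9%, 0.5/2.65 = 19% and 1.0/2.65 = 38% of it. These shifts are assumptions and say nothing about what is likely.

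**The case against.** The strongest reply is that the office has little leverage. Every registered patient is invited, patients apply on their own initiative and are blinded, the assistant is called independent, and the arm follows automatically from the practice. All of this stands and narrows the concern to rejection and timing. It does not mask the decision, and independence does not help if the same role knows the sequence.

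A second reply is that the wording is loose. The office has several research assistants, the word participants may also cover providers, and the full protocol may separate the tasks. That is possible. But the article does more than leave a detail out: it names one role for all three tasks and says allocation is open to the researchers.

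A third reply is that back beliefs, pain and function are measured at baseline and an adjusted analysis is planned. This protects against selection on those variables in that analysis only.

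Three stronger readings are tempting but unsupported:

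- A reader might infer from "serious long existing comorbidity" that the exclusions invite subjective judgement. The sentence goes on to a closed list of named diseases, and the office is not asked to separate specific from nonspecific back pain, because patients must already be "are diagnosed with nonspecific LBP".
- A reader might infer that having only four randomised units makes this worse. Selection after randomisation would not average out with any number of clusters.
- A reader might infer that the assistant can place individual patients in an arm at will. Automatic assignment by practice rules that out, except through the date of inclusion.

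One limit also counts against the remedy. Unblinded GPs and PTs may influence who is diagnosed or encouraged to apply, and masking the office screener cannot prevent that.

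**Conclusion.** The concern holds in a limited form. As written, the plan lets the role that knows the rollout order decide whether and when an applicant is included. The office-level risk is selective rejection, or delayed or advanced inclusion near a crossover. Either could produce a before-to-after change in case mix within a cluster, which cluster fixed effects do not remove and to which the crude analysis is exposed. This is a risk created by the arrangement and is not evidence that bias occurred. Its size cannot be estimated from the documents. The conclusion assumes that participants in the role description includes patients, as the Study design and Patients sections suggest, and that no separation of tasks exists beyond what the article states. The change is worth making because it is cheap and leaves the design, the sample size and the analysis as they are.

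**What to change.** Using the research assistants already in place:

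1. Have eligibility recorded against the listed criteria by an assistant who does not hold the sequence, and before the practice is looked up.
2. Set the arm by the practice's status on a date the assistant cannot influence, such as receipt of the application. Speed of handling then no longer decides the arm.
3. Send the invitation letters on the same schedule in all clusters, whatever their training date.
4. Log the numbers invited, applied, ineligible (with reason) and enrolled, by cluster and period. This cannot prevent selection through unblinded GPs and PTs, but it makes it visible.

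The cost is a revised form and workflow and a small administrative delay per applicant. Where a recent visit to a participating practice has to be verified, that check comes after the other criteria are recorded.

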### Statistical methods

Data on outcome measures will be gathered at baseline, at 3, 6, and 12 months follow-up. Data will be compared between intervention and control group. Two (longitudinal) analyses will be performed: 1) a crude analysis of outcome measures, and 2) an analysis of outcome measures adjusted for prognostic dissimilarities, confounding, and effect modification. Multilevel analyses will be performed to take into account repeated measurements in participants as well as the effects of clustering in this study. Clusters will be taken into account in this analysis as fixed effects. All analyses will be performed according to the intention-to-treat principle. Multilevel analyses will be performed using MlWin 2.0. Linear and logistic regression analyses will be performed using SPSS.

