**Fig. 2 Fig2:**
[figure not shown]
Conceptual model of the multifaceted implementation strategy

Further strengths of the present study include the stepped-wedge cluster randomised design. Because every cluster serves as its own control, but also as control for other clusters, this design allows both between group analyses as well as within-group analyses. Using this design, all clusters will have received the intervention at the end of the study, and thus, participation in this study will be higher. Clustering the participating HCPs allows for prevention of contamination between intervention and control group. Furthermore, this design allows the adaptation and improvement of the intervention strategy based upon experiences gathered during the stepwise implementation process.

Although the stepped-wedge design has shown to be a robust way of evaluating intervention effectiveness in implementation research [37], the current study will likely face some methodological challenges as well. At each point where a new cluster receives the intervention, data collection will be necessary, making this a time-consuming logistical challenge. Furthermore, the analysis of the gathered data will be complex due to these repeated measures in same participants. Inherent to the timing of the intervention rollout being the unit of randomisation, it will be impossible to blind researchers and participating HCPs for sequence allocation.

By combining the results of the intervention effects with the results of the process evaluation, this study will provide insight into the (cost-) effectiveness of the multifaceted implementation strategy as well as insight into patient and HCP experiences with this strategy. The subsequent qualitative subgroup analysis will give insight into the experiences of patients of various ethnic backgrounds with the current implementation strategy. The valuable information gained with this study may prove useful for policy-makers, health care providers, and other researchers who are in the process of reducing the burden of back pain on individuals and societies.

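### The stated stepped-wedge analysis names no calendar-period term, so the crude comparison is confounded with time and the adjusted one is protected only if period is among its unspecified confounders

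*Protocol article*

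**What the plan says.** The Study design section identifies the trial: "This study is a stepped-wedge cluster-randomised controlled trial". It describes four clusters formed by geography. The Randomisation section adds: "The clusters sequentially receive the intervention". What is randomised is the moment at which each cluster starts.

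Patients take the status of their practice when they enrol. In the article's words, "patients registered within a practice that is in the control group at time of enrolment will automatically be allocated into the control group for patients".

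Statistical methods gives the comparison, "Data will be compared between intervention and control group", and announces two longitudinal analyses. One is crude. The other is adjusted for prognostic differences, confounding and effect modification, and no variables are listed. Multilevel models handle the repeated measurements and the clustering, and "Clusters will be taken into account in this analysis as fixed effects". The measurement times are baseline and 3, 6 and 12 months.

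The Discussion counts it as a strength of the design that it permits both between-group and within-group analyses: "Because every cluster serves as its own control, but also as control for other clusters". Its list of methodological challenges covers data collection, repeated measures and blinding. Time trends are not on it.

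**The concern.** In a stepped wedge, control observations are mostly early and intervention observations mostly late. Randomising the order of rollout does not remove this; it only decides which cluster goes first. Intervention is separated from time by comparing clusters that have and have not crossed over in the same period, and the model does that only if it contains period.

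The article says how clusters and repeated measures enter the model but not how calendar time does. The 3, 6 and 12 month times run from each patient's own baseline and cannot stand in for it. Once clusters are fixed effects and period is absent, each cluster contributes only its later observations minus its earlier ones. A change over the study in recruitment mix, season or general uptake of the 2010 guideline could then look like an effect, or hide one.

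The primary outcome is exposed. So are the cost and effect differences that the Economic evaluation section divides to obtain its ratios, and the 5-year budget impact built on them.

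**Working it through.** **Inputs from the article.** Four clusters (Study design). Mean 26.5, SD 6, a 10% improvement, 500 patients and 20% dropout (Sample size). The target difference is 0.10 × 26.5 = 2.65 points, and 500 × 0.80 = 400 patients are analysable.

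**Assumptions.** The design figure is not available, so I take 5 periods with one crossover per step and equal cells: 400 / (4 × 5) = 20 patients per cell. One follow-up score per patient, SD 6, no true effect, and a linear trend of g points per step. The article gives no g, so a range is shown.

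**Bias without cluster terms.** Number the periods 0 to 4.
- The 10 intervention cells have mean period (1×1 + 2×2 + 3×3 + 4×4)/10 = 3.0.
- The 10 control cells have mean period (4×0 + 3×1 + 2×2 + 1×3)/10 = 1.0.
- Bias = (3.0 − 1.0)g = 2.0g.

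**Bias with cluster fixed effects, no period.** In the first cluster to cross, intervention periods average 2.5 and control periods 0. In the second they average 3.0 and 0.5. The gap is 2.5 in all four clusters, so bias = 2.5g.

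**With period fixed effects** the bias is 0.

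**Standard errors.** SE = SD / √(20 × R), where R is the residual sum of squares of intervention status over the 20 cells.
- Cluster effects only: R = 0.8 + 1.2 + 1.2 + 0.8 = 4.0, so SE = 6/√80 = 0.67.
- Cluster and period effects: R = 10 − 30/5 − 30/4 + 100/20 = 1.5, so SE = 6/√30 = 1.10.
- Variance ratio: 4.0/1.5 = 2.67.

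**Type I error** with cluster effects and no period = Φ(b/SE − 1.96) + Φ(−b/SE − 1.96), with b = 2.5g and SE = 0.67.

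| g per step | Bias b | Share of 2.65 | Type I error |
|---|---|---|---|
| 0.125 | 0.31 | 12% | 7.5% |
| 0.25 | 0.63 | 24% | 15% |
| 0.5 | 1.25 | 47% | 46% |

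**Another layout.** With 4 periods, no all-control period and 25 patients per cell, the slopes are 1.33g without and 2.0g with cluster effects. The same three trends then give type I error of about 6%, 10% and 26%.

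**If the baseline is used.** Suppose each follow-up falls a fixed interval after a baseline that carries the same linear trend.
- Change from baseline: every patient's change contains the same amount of drift, so the bias is about 0.
- Baseline as covariate, with baseline to follow-up correlation ρ: bias is about 2.5g(1 − ρ) and SE about 0.67 × √(1 − ρ²). For an assumed ρ of 0.5 to 0.7, g = 0.25 gives a bias of 0.31 to 0.19 and type I error of about 8% to 7%. For g = 0.5 the bias is 0.63 to 0.38 and type I error about 19% to 12%.

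**The case against.** The strongest reply is that a design article is condensed and that a covariate list belongs in an analysis plan that is not shown. The adjusted analysis covers confounding, and calendar time is a confounder here. This stands in part. A reader might infer that both declared analyses leave period out; for the adjusted one the text does not settle the matter. It does not rescue the crude analysis, which is unadjusted by its own description. Nor is period an optional covariate in this design, and the article specifies other structural terms while omitting this one.

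The second reply is that follow-up scores analysed alone are a worst case, because the article plans a baseline and longitudinal analyses. This stands, and it is why the table is an upper end. A reader might infer that any secular trend passes in full into the estimate. That is not so for a linear drift under change from baseline. However, the article does not say how baseline enters the model, and a non-linear trend could still cause bias.

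Two further inferences are tempting and unsupported.
- That the standard error without period is wrong. With g = 0 the model without period has type I error of about 5%, so 0.67 is correct for that model. The inflation in the table comes from bias.
- That a before-after effect estimate is planned. The Discussion sentence describes what the design permits; it does not announce such an estimate.

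**Conclusion.** The point holds. Exposure is tied to calendar time by the rollout and by allocation at enrolment, and the stated analysis names nothing that separates the two. The crude analysis is confounded with time; for the adjusted analysis, protection depends on a choice the article does not record.

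The tabulated sizes rest on an assumed layout, equal cells, one follow-up score per patient and a linear trend whose size the article does not give. They show that a modest drift could matter against a 2.65-point target. They do not show that such a drift exists. That the bias arises when period is absent does not depend on these assumptions; its size does.

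**What to change.** State calendar period (trial step) as a categorical fixed effect in both the crude and the adjusted between-group models, alongside intervention status, cluster and time since enrolment. Use the same adjustment for the cost and effect differences that feed the economic evaluation.

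This takes one categorical term, built from dates already recorded, and no new data. The price is precision: in the assumed layout the SE rises from about 0.67 to about 1.10. Power for 2.65 points is then Φ(2.65/1.10 − 1.96), about 0.68, against about 0.98 without period; using the baseline would recover part of this. The larger SE is the cost of separating intervention from time, not the repair of a faulty one. The planned power of 0.90 should be rechecked under the model with period, using the actual layout.

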#### Economic evaluation

An economic evaluation will be performed to measure and analyse the cost differences between the current implementation strategy and passive dissemination of the guideline in relation to the effect differences between the two groups. Direct costs related to health care utility as well as indirect costs related to productivity losses due to absenteeism and presenteeism will be analysed. Costs of the implementation strategy will be measured, valued and analysed using a bottom-up approach. Health care consumption and productivity losses will be valued using Dutch guideline prices.

Cost-effectiveness and cost-utility analyses will be performed from a societal perspective. Functional status and quality of life of the patients will be taken as outcome measures for the economic evaluation. To calculate incremental cost-effectiveness ratios (ICER) and cost-utility ratios, the differences in mean costs between the two groups will be divided by their differences in outcome measures. Confidence intervals (95 %) will be estimated using bootstrapping methods with a minimum of 5.000 replications [23]. Uncertainty of the ICERs will be graphically presented in a cost-effectiveness plane (CE plane), as well as cost-effectiveness acceptability curves (CEAC) [24, 25].

At last, a budget impact analysis will extrapolate the results of the economic evaluation to a period of 5 years in order to estimate the financial costs of applying this implementation strategy on a larger scale. This analysis will be performed from several perspectives (i.e., societal, government, and insurance) and several scenarios for application of this implementation strategy.

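### The cost-effectiveness ratio is set out as a two-group difference with no calendar-period term, which leaves it open to confounding by time in this stepped-wedge design

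*Protocol article*

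**What the plan says.** All references are to the protocol article.

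- **Economic evaluation**, on the ratio: "the differences in mean costs between the two groups will be divided by their differences in outcome measures". On the effects used: "Functional status and quality of life of the patients will be taken as outcome measures for the economic evaluation". On uncertainty: "Confidence intervals (95 %) will be estimated using bootstrapping methods with a minimum of 5.000 replications", followed by a cost-effectiveness plane and acceptability curves. A budget impact analysis then projects the results over 5 years.
- **Study design**, on the clusters: "The HCPs are allocated to one of four clusters, which are compiled based on the HCPs’ geographic proximity to each other". On how patients get their group: "patients registered within a practice that is in the control group at time of enrolment will automatically be allocated into the control group".
- **Randomisation**, on the rollout: "The clusters sequentially receive the intervention, and the moment of intervention rollout within one cluster the unit of randomisation is".
- **Statistical methods**: "Multilevel analyses will be performed to take into account repeated measurements in participants as well as the effects of clustering in this study", and "Clusters will be taken into account in this analysis as fixed effects". A crude analysis is planned, and a second one adjusted for confounding among other things.

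Neither Statistical methods nor Economic evaluation names step, period or calendar time as a model term. The economic section does not say whether its differences are adjusted, and it names no resampling unit.

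**The concern.** The ratio is described as it would be for a parallel-group trial. Here, group and calendar time are linked by design: control patients come mainly from the early part of the study and intervention patients from the later part. The two groups also differ in cluster mix, since the first cluster to cross over supplies mostly intervention patients and the last mostly controls.

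If care volume, work absence, functional status or quality of life drifts over the study for reasons unrelated to the intervention, a simple comparison of group means credits the drift to the intervention. It can do so in both the numerator and the denominator, and so in everything built on them. Cost-effectiveness is in the title and the primary objective, and the projection over 5 years would carry any such error forward.

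A smaller second question is whether the bootstrap keeps the clustering that the outcome analysis promises to handle.

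**Working it through.** The economic section states no numerical result to reproduce, so the check is on how the stated rule behaves in this design.

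**1. Link between group and time.** Fig. 1 is not available in the text, so I assume a standard wedge: 4 clusters, 5 periods, equal cells, new patients in each period. Cluster k is in control up to period k and in intervention after it.

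- Mean period of the 10 intervention cells: (14 + 12 + 9 + 5)/10 = 4.0.
- Mean period of the 10 control cells: (1 + 3 + 6 + 10)/10 = 2.0.
- Gap: 2 periods. A linear trend of 1, 2 or 5 units per period adds 2, 4 or 10 units to the difference.
- Range: without the last, all-intervention period, the gap is 20/6 − 20/10 = 1.33. Without the first, all-control period (remaining periods renumbered 1 to 4), it is 30/10 − 10/6 = 1.33.

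**2. Would cluster terms alone remove it?** No. Within each cluster, mean intervention period minus mean control period is 3.5 − 1 = 2.5, 4 − 1.5 = 2.5, 4.5 − 2 = 2.5 and 5 − 2.5 = 2.5. With cluster fixed effects and no period term, the trend would enter 2.5 times.

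**3. Would cluster and period terms remove it?** Yes. The simulation used 2,000 runs, 25 patients per cell, ICC 0.05 at cluster level, no true effect and a trend of 0.1 SD per period. The unadjusted difference averaged 0.196 SD. The estimate with cluster and period terms averaged −0.003 SD. The standard errors were 0.134 and 0.155 SD.

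**4. If the bootstrap ignored clustering.** Each cluster's share of the intervention group is 0.4, 0.3, 0.2, 0.1, and of the control group 0.1, 0.2, 0.3, 0.4. The squared differences sum to 0.09 + 0.01 + 0.01 + 0.09 = 0.20. With total variance 1, N patients in two equal groups and ICC ρ:

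- naive variance = 4/N;
- true variance, ICC at four-cluster level = 4(1 − ρ)/N + 0.20ρ;
- true variance, ICC at practice level = 4(1 − ρ)/N + 0.20ρ/p, with p practices per cluster (equal sizes, no further cluster variance).

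The article's ICC of 0.05 is for back beliefs. It gives none for costs, functional status or quality of life, and it does not state the level. N = 400 is 500 less 20% dropout. p = 6.25 for 25 GP practices; p = 11 for 44 GP and physiotherapy practices.

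| Level of ICC 0.05 | N | True / naive variance | SE ratio | Coverage of nominal 95% |
|---|---|---|---|---|
| Four clusters | 400 | 0.0195 / 0.0100 | 1.40 | 84% |
| Four clusters | 500 | 0.0176 / 0.0080 | 1.48 | 81% |
| 25 practices | 400 | 0.0111 / 0.0100 | 1.05 | 94% |
| 25 practices | 500 | 0.0092 / 0.0080 | 1.07 | 93% |
| 44 practices | 400 | 0.0104 / 0.0100 | 1.02 | 94% |
| 44 practices | 500 | 0.0085 / 0.0080 | 1.03 | 94% |

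Coverage here leaves out any time bias.

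**5. Which level the sample size suggests.** A difference of 2.65 (10% of 26.5), SD 6, two-sided alpha 0.05 and power 0.90 need 108 per arm, 216 in total. With 20 patients per unit (500/25 GP practices), the design effect is 1 + 19 × 0.05 = 1.95 and N = 421. That is 505 after multiplying by 1.2 for dropout, or 527 after dividing by 0.8. With 125 per unit (four clusters), the design effect is 7.2, N = 1,555, and 1,944 after dividing by 0.8. The stated 500 therefore fits an ICC at practice level, not at four-cluster level.

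**The case against.** The strongest reply is that a cost difference over an effect difference is simply what such a ratio is, and model-adjusted differences can fill it. The economic section is a subsection of Statistical methods, which commits the study to multilevel handling of clustering and to an analysis adjusted for confounding. Functional status, quality of life, care use and productivity loss are all listed as patient outcomes, so they fall within that commitment. The resampling unit is a detail that a design article commonly leaves to the full plan.

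Much of this stands. A reader might infer that the article prescribes unadjusted differences and resamples patients as if independent, so that the intervals are too narrow. The article says neither; both would be read out of its silence. A reader might also take 84% coverage as the expected result, but that needs the ICC of 0.05 to sit at the level of the four clusters, and the sample size suggests otherwise. Nor should price and reimbursement drift be blamed: the article values care use and productivity loss at Dutch guideline prices, which largely removes it. Volume trends remain.

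What the reply does not meet is the time term. Confounding is mentioned only in general, for the second of two analyses, and period is not named. As step 2 shows, the one design term that is named, cluster, does not remove a trend. The same gap affects the main effectiveness analysis, so the remedy belongs in both places.

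**Conclusion.** The point holds in limited form. The only stated definition of the ratio is a two-group difference, group is tied to enrolment time, and no period term is named. The ratios, plane and acceptability curves are therefore open to confounding by secular trends. They are not shown to be confounded: bias needs an actual trend, and the document gives none.

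Under the assumed five-period wedge, a per-period trend enters each difference about twice (1.33 times in the shorter layouts). The effect on the ratio itself cannot be computed, because the article gives no cost figures, no ICC for costs and no trend.

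On clustering, the supportable statement is only that carry-over to the bootstrap is not stated. If clustering were ignored, the loss would be small with the ICC at practice level and material with it at the level of the four clusters.

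**What to change.** In Economic evaluation, state that incremental cost and incremental effect are estimated jointly (for example by seemingly unrelated or bivariate mixed regression) from models with cluster and calendar-period terms. State a bootstrap that respects clustering: resample practices within cluster, or use a model-based method. Resampling only the four clusters would be unreliable. Build the ratios, the plane and the acceptability curves from those adjusted replicates. Name the period term in Statistical methods as well, so that the two sections agree.

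The cost is a few sentences and some extra programming, with no new data. Intervals will be wider: in the simulation the standard error with cluster and period terms was 0.155 SD, against 0.134 SD for the unadjusted difference.
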